### Methods for additional analyses (e.g. subgroup analyses) {20b}

Regression analysis is used to explore any relationships between patient characteristics and outcome. Depending on the characteristics of the outcome, different concepts for regression analyses are used. Linear regression is used for continuous variables, logistic regression for dichotomous variables and ordinal regression for ordinal outcome variables.

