## Introduction

### Background and rationale {6a}

Parastomal hernia is the main complication of an enterostoma [1–3]. Occurrence rates up to 80% have been reported, with numbers varying considerably due to differences in diagnostic method, follow-up time, type of stoma, and the lack of a uniformly accepted definition of parastomal hernia [2–5]. Symptoms from a parastomal hernia range from asymptomatic to problems significantly impairing the patient’s quality of life, even life-threatening due to strangulation of the hernia content. There are few studies investigating the frequency of specific complaints, and there is thus little information clearly indicating which patients are likely to benefit from surgical repair [6].

Several techniques are presently used for parastomal hernia repair. The European Hernia Society recommends a synthetic mesh plasty, but scientific evidence on how and in what position the reinforcing material should be applied is weak. Even the best available methods today are associated with high recurrence rates and significant risk for complications that can be fatal [7–9]. The use of synthetic mesh material is associated with severe complications such as mesh infection, fistula formation and erosion of the intestines [9]. There are also patient associations and other communities that oppose the use of synthetic mesh material (https://www.facebook.com/groups/meshproblems/, https://www.facebook.com/MeshMeNot/, https://meshmenot.wordpress.com/, https://meshvictimsunited.org/).

Autologous full-thickness skin grafting (FTSG) has been shown to be a possible alternative to conventional synthetic mesh in hernia repair [10]. By avoiding the use of foreign materials, FTSG could offer safer and less expensive reinforcement in parastomal hernia repair. The technique of grafting autologous skin in hernia repair was successfully used before the advent of synthetic mesh, but its application in parastomal hernia is new [11, 12].

The present RCT follows a translational chain of research starting with a murine model which showed good FTSG survival in both intraperitoneal and onlay positions [13]. Furthermore, in an experimental model, fresh FTSG was shown to have equal or better tensile strength than both synthetic and biological reinforcement material, which is a prerequisite in hernia surgery [14].

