### Implementation {16c}

The allocation sequence is generated by the research group administrators. Patients are enrolled by surgeons at the out-patient clinic and are provided a randomisation number correlating to a sealed envelope. The intervention arm is assigned after induction of anaesthesia when the accompanying randomisation envelope is opened.

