## Data collection and management

### Plans for assessment and collection of outcome data {18a}

All clinical study data will be registered in an Access® database (Microsoft, Redmond, WA, USA).
Baseline data are collected at the time of inclusion once assessment of eligibility by the including surgeon is complete. At this point, the surgeon is unaware of what intervention the patient will be allocated. Baseline data include:
BMI. Body mass index.ASA (American Society of Anesthesiologists) class.Current medical conditionsCurrent medicationNumber and type of previous abdominal surgeries.Type of and reason for stomaOperation data will be collected immediately after surgery by the surgeon. Data collected on completion of surgery:
Participating surgeonsTreatment allocationSize of the hernia defect before and after reductionSize of the FTSGLength of stoma bowel above the fasciaOperating timeMinimum overlap of reinforcement materialData on postoperative care on the ward will be collected by the blinded nursing staff on a case report form (CRF). After discharge, the CRF will be collected and registered in the database. Parameters monitored daily during the entire time on the ward:
C-reactive proteinSerum albuminComplete blood cell countSerum creatinineBlood glucoseOxygen saturationExperienced pain assessed on a visual analogue scaleClinical follow-up data will be collected by the blinded surgeon conducting the follow-up. This surgeon will be experienced in stoma surgery (i.e. colorectal, or abdominal wall surgery) but will not receive any specific training on the follow-up procedure in this study. Parameters that will be assessed at the clinical follow-up:
BMIClinically judged recurrenceSurgical complication (seroma, infection, other)Stoma complication (stenosis, necrosis, other)Readmission or reoperation during the follow-up periodPain assessed on a visual analogue scaleExperienced improvement assessed on a visual analogue scaleAbnormal healing process or poor aesthetic result of the operation scarCompliance to the postoperative girdle prescribedQuestionnaires both preoperative and during the follow-up period will be collected by the research group administrators and stored in a separate Access database. Questionnaires used in the study are:

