#### Rate of complications and recurrences

Data are presented descriptively and the results from each study group are compared with chi-squared test.

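### Complications and recurrence are compared without covariate adjustment although stoma type and BMI are recorded before allocation: a valid test, but some precision may be given away cheaply

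*Protocol article*

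**What the plan says.** **Treatment comparison.** Under Rate of complications and recurrences, "the results from each study group are compared with chi-squared test". No covariate enters. The general paragraph under {20a} names only chi-squared, Mann-Whitney and t tests.

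**Regression.** It appears only under additional analyses {20b}: "Regression analysis is used to explore any relationships between patient characteristics and outcome". No covariates are listed and no adjusted treatment effect is described.

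**Baseline data.** Under {18a}, "Baseline data are collected at the time of inclusion once assessment of eligibility by the including surgeon is complete", and "At this point, the surgeon is unaware of what intervention the patient will be allocated". The list includes "BMI. Body mass index.ASA (American Society of Anesthesiologists) class" as well as stoma type. Section {16c} then states: "The intervention arm is assigned after induction of anaesthesia when the accompanying randomisation envelope is opened". These variables therefore precede allocation.

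**Allocation.** Sections {16a} and {16b} describe blocks of five and a single series of 90 numbered envelopes. There is a remark about balance at low-volume centres, but no stratification factor is named, and nothing balances stoma type or BMI. The eligibility criteria {10} admit three stoma types.

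**The concern.** The trial is small, and its patients differ in stoma type and build. Allocation does nothing to balance these features, and the named analysis does not use them, although they will already be in the database as clean pre-allocation values. If they predict complications, an unadjusted comparison gives a less precise estimate than the same data could yield. A chance imbalance in the one trial actually run would also stay uncorrected in the reported difference.

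This is a choice that the article makes and not a detail that it leaves open: it names the method for the treatment comparison and assigns regression to another purpose.

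**Working it through.** **1. The plan's own figure.** Inputs from {14}: 15% against 40%, 80% power, 39 per arm, 45 per arm enrolled; the level of 0.05 is in {20a}. The pooled-variance formula is n = [z_α √(2·0.275·0.725) + 0.8416 √(0.15·0.85 + 0.40·0.60)]² / 0.25².
- One-sided 5%: (1.645·0.6315 + 0.8416·0.6062)² / 0.0625 = 38.4, so 39. This matches the plan.
- Two-sided 5%: (1.960·0.6315 + 0.8416·0.6062)² / 0.0625 = 48.9, so 49.

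Exact power of the two-sided chi-squared test is 72.3% at 39 per arm and 78.4% at 45. The sidedness of the calculation is a separate matter. Here it shows only that there is no spare power.

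**2. Expected events.** 39 × (0.40 + 0.15) = 21.5 and 45 × (0.40 + 0.15) = 24.8. A model with three terms (arm, a two-level stoma type, BMI) has about 7 to 8 events per term, so the covariate list must be short.

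**3. Chance imbalance.** Take a factor carried by half the patients (assumed) and 45 per arm. The SD of the difference in prevalence is √(2·0.25/45) = 10.5 points. A gap of 15 points or more has probability 15% by normal approximation, 17% by exact binomial, and 21% if exactly 45 of the 90 are carriers.

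**4. What such a gap does.** With an average risk of 27.5% and half the patients carriers, an odds ratio (OR) of 2 implies risks of 20.7% and 34.3%. An OR of 3 implies 17.0% and 38.0%. A 15-point gap moves the risk difference by 0.15 × 13.6 = 2.0 points or 0.15 × 21.0 = 3.2 points. The planned difference is 25 points.

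**5. Gain from adjustment.** Two simulations held the marginal rates at 40% and 15%. All covariate strengths are assumed.

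*One standardised prognostic score, 6,000 trials per cell, two-sided chi-squared against adjusted logistic test:*

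| OR per SD | 39 per arm | 45 per arm |
|---|---|---|
| 1.0 | 72.0% → 71.9% | 78.9% → 78.2% |
| 1.5 | 73.5% → 74.8% | 79.3% → 80.3% |
| 2.0 | 71.8% → 75.5% | 77.4% → 80.4% |
| 3.0 | 73.6% → 81.0% | 78.5% → 84.8% |

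The standardised risk difference gave almost the same power.

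*A binary covariate (55% prevalence, standing for stoma type) and a continuous one (standing for BMI), 4,000 trials per scenario:* with ORs of 3 and of 2 per SD, the variance of the risk difference falls by 8 to 9%. Power rises from 71.5% to 76.2% (39 per arm) and from 78.9% to 82.5% (45 per arm). With ORs of 2 and 1.4, the variance ratio is 0.99 to 1.01 and the gain is about 1 to 2 points.

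**6. Type I error.** The chi-squared test held 4.8 to 5.6% across the simulations. The adjusted estimate with a simple robust standard error gave 5.2 to 6.0% in one run of the two-covariate setting and 6.3 to 6.5% in another.

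**The case against.** The strongest reply is that nothing is wrong with the stated test. Under randomisation without strata, the unadjusted chi-squared test keeps its error rate, and chance imbalance is already part of its sampling error. An unadjusted primary analysis is a legitimate choice. This stands: a reader might infer that the comparison is biased or invalid, and neither the documents nor the simulations support that.

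A reader might also take the Background as evidence that stoma type is prognostic, since it speaks of "numbers varying considerably due to differences in diagnostic method, follow-up time, type of stoma". That sentence explains why reported occurrence of parastomal hernia differs between studies. It does not concern complications or recurrence after repair, and every trial patient already has a hernia. No section says that BMI predicts either outcome. The benefit is therefore undocumented and could be close to nil.

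It is tempting, too, to fault the exploratory regression for generating false-positive predictors. The documents do not support that. The section is labelled additional, claims nothing confirmatory, and gives no number of tests from which to compute an error rate. Which terms enter such models is commonly left to a fuller document.

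Finally, adjustment has its own small cost: the type I error in step 6. Analysing per protocol and planning no method for missing data are separate matters, which adjusting for two covariates would not cure.

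What remains is that suitable pre-allocation data are collected, allocation does not use them, and the named treatment comparison does not use them either.

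**Conclusion.** The point holds as a cheap improvement in efficiency and robustness, not as an error in the test. At 39 to 45 per arm the power gain is about 0 to 2 points for weak covariates and about 4 to 7 points for strong ones, with intermediate strengths in between. An imbalance of 15 points in a common factor would shift the risk difference by about 2 to 3 points under the assumed ORs of 2 to 3. All these sizes rest on assumed prognostic strength and on the planned rates of 40% and 15%. Nothing has been calculated for recurrence, because the article gives no recurrence rate.

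**What to change.** Before any comparison by arm is made, add to the statistical methods a covariate-adjusted treatment estimate for complications: a standardised risk difference with 95% CI from a logistic model with arm, stoma type and BMI only. Fix the coding of stoma type in advance. The documents give no basis for pooling particular types, and each extra level uses scarce events. Use a permutation p-value or a small-sample standard error, and report the unadjusted chi-squared result alongside. Apply the same approach to recurrence if there are enough events. The exploratory regression in {20b} can stay as it is.

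Naming the model beforehand matters because section {17a} says that the data analysts are not blinded.

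The cost is a few sentences and a few lines of code, with no new data. The downside is a negligible gain if the covariates prove weak and, if the small-sample correction is omitted, a type I error of up to about 6.5%.

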### Statistical methods to handle protocol non-adherence and missing data {20c}

Study outcomes are analysed as per protocol. Patients are randomised in the operating theatre after induction of general anaesthesia and the only scenario where the patient does not receive the intervention allocated is if it is deemed technically impossible after the laparotomy has been performed or if the patient suffers an anaesthetic complication before the randomisation envelope is opened. In both these scenarios, the patient cannot be operated with any intervention so chance should evenly distribute this specific form of non-adherence.

No statistical methods are used to compensate for missing data or loss to follow-up. The power calculation is dimensioned to enable enough statistical power with up to 12 missing patients in all.

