### Trial design {8}

The trial is a parallel group, superiority trial with an allocation ratio of 1:1.

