### Criteria for discontinuing or modifying allocated interventions {11b}

Any study patient requesting to end their participation in the study will immediately be withdrawn from whatever stage they have reached in the study process without having to explain why.

The anatomy in the abdominal cavity as well as the current conditions at the time of surgery can prevent the feasibility of the planned procedure, in part or completely. Minor alterations to the surgical interventions may be accepted, such as isolated deviations from the specified intervals when suturing the reinforcement material to the abdominal wall. Major obstacles that make the planned procedure impossible to perform without significant risk, such as massive adhesions or other contraindications such as finding disseminated malignancy, will exclude the patient from further participation in the study.

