## Outcomes {12}

### Participants will be followed up at 3, 12 and 36 months postoperatively.

#### Primary outcome:

Rate of surgical complications at 3, 12 and 36 months. Complications will be assessed over a 3-year period at regular follow-ups by an independent surgeon who is unaware of which surgical method was used. Eventual complications include infection, bleeding, seroma, and fistula formation. Regarding recurrence, the best available methods of repair today are associated with complications that in some cases can be fatal [7].

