## Assignment of interventions: blinding

### Who will be blinded {17a}

The allocated intervention is blinded to the patient, postoperative care providers and the surgeon performing the clinical follow-ups. The operating surgeons and the data analysts are not blinded.

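### The complication comparison is per protocol only and drops patients excluded after the envelope is opened by a surgeon who knows the arm, so chance cannot be relied on to balance them

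*Protocol article*

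**What the plan says.** Trial design {8}: "The trial is a parallel group, superiority trial with an allocation ratio of 1:1". The primary outcome is "Rate of surgical complications at 3, 12 and 36 months".

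The section on non-adherence and missing data {20c} sets the analysis population: "Study outcomes are analysed as per protocol". The article names no intention-to-treat analysis. The section recognises two ways in which a patient may not receive the allocated repair. One is an anaesthetic complication before the envelope is opened. The other is that the repair is not done "if it is deemed technically impossible after the laparotomy has been performed". It then argues: "In both these scenarios, the patient cannot be operated with any intervention so chance should evenly distribute this specific form of non-adherence".

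The section on discontinuing or modifying interventions {11b} says that major obstacles to the planned procedure, with massive adhesions, disseminated malignancy and other contraindications as examples, "will exclude the patient from further participation in the study".

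On timing and blinding: "The intervention arm is assigned after induction of anaesthesia when the accompanying randomisation envelope is opened" (Implementation {16c}), and "The operating surgeons and the data analysts are not blinded" (Who will be blinded {17a}).

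**The concern.** A superiority test is protected by randomisation only if the groups compared are the groups randomised. Here some patients can leave the comparison after allocation, through a judgement made by someone who knows the allocation. If the threshold for abandoning the repair differs between arms, and the patients removed differ in risk from those who stay, the complication rates are no longer comparable and the type I error is no longer the nominal one. The outcome at stake is the primary one, and it is a safety outcome. The patients removed have already had an anaesthetic and a laparotomy. In the FTSG arm they may also have a donor wound, because the intervention description {11a} places graft excision before the laparotomy.

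**Working it through.** **Step 1. When is the exclusion decided, and by whom?** The envelope is opened after induction {16c}. The post-laparotomy judgement comes later {20c}. The operating surgeon is not blinded {17a}. This exclusion is therefore after allocation and made with the arm known. The anaesthetic scenario occurs with the envelope still sealed, so allocation cannot influence it.

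**Step 2. Does the protocol's premise hold?** Section {20c} assumes that an excluded patient could have had neither repair. Section {11b} does not require that. Its test is whether the planned procedure can be done without significant risk, and its list is open-ended. The planned procedure differs by arm. An exclusion can satisfy {11b} without satisfying the premise in {20c}.

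**Step 3. What is lost?** Section {18b} keeps data collected before discontinuation, and {22} sends complications to the case report form. After discontinuation nothing more is collected {18b}, no method is used for missing data {20c}, and the patient is outside the per-protocol comparison.

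**Step 4. The plan's own figures.** Inputs from Sample size {14}: 15% against 40%, 80% power, significance level 0.05. The pooled formula is n = [z_α·√(2·p̄·(1−p̄)) + z_β·√(p1(1−p1) + p2(1−p2))]² / (p1−p2)², with p̄ = 0.275.
- One-sided: (1.645 × 0.6315 + 0.842 × 0.6062)² / 0.0625 = 38.4, so 39 per arm, as stated.
- Two-sided: (1.960 × 0.6315 + 0.842 × 0.6062)² / 0.0625 = 48.9, so 49.

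The 39 reproduces only one-sided, and the protocol states no sidedness. Both bases are therefore shown in step 6. The allowance for loss agrees with {20c}: 90 − 2 × 39 = 12.

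**Step 5. Illustration of bias. All inputs are assumptions except the 45 per arm.** No true difference; complication rate 27.5% in both arms, the midpoint (15 + 40)/2; a fraction d of patients is difficult, with risk q; a share f of these is excluded in a given arm. The per-protocol rate in that arm is (0.275 − d·q·f)/(1 − d·f). The test is the uncorrected chi-squared at two-sided 0.05. Rejections are by simulation, and repeat runs differ by about 0.1 percentage point.

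| d = 10% | FTSG rate | Mesh rate | False 'FTSG safer' |
|---|---|---|---|
| No exclusions | 27.5% | 27.5% | 2.7% |
| q = 70%, all excluded in both arms | 22.8% | 22.8% | 2.6% |
| q = 70%, 75% excluded in FTSG, 25% in mesh | 24.1% | 26.4% | 4.4% |
| q = 70%, all excluded in FTSG only | 22.8% | 27.5% | 7.1% |
| q = 70%, all excluded in mesh only | 27.5% | 22.8% | 0.7% (false 'mesh safer' 7.1%) |
| q = 40%, all excluded in FTSG only | 26.1% | 27.5% | 3.4% |

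Example for the fourth row: (0.275 − 0.10 × 0.70)/(1 − 0.10) = 0.205/0.90 = 22.8%.

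**Step 6. Cost of analysing as randomised.** Assume k patients per arm get neither repair and have complication rate c in both arms. Each arm's rate becomes ((45 − k)·p + k·c)/45. With k = 4 and c = 27.5% the rates are 16.1% and 38.9%; with c = 60% they are 19.0% and 41.8%. Power at 45 per arm falls from 85.4% to 77–79% one-sided, and from 76.6% to 66–68% two-sided.

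**The case against.** The best defence is that the two operations are alike. They share the laparotomy, adhesiolysis, stoma dissection, fascial reduction and suturing to the abdominal wall {11a}, and the comparator was chosen for its similarity {6b}. Massive adhesions and disseminated malignancy are not specific to an arm. The obvious graft-specific obstacles, lack of suitable skin and donor-site morbidity, are screened out at enrolment {10}. Exclusions may therefore be few and balanced, and equal exclusions leave the error rate where it was. All of this stands, and it limits how large the problem is likely to be. It does not restore the assurance, because the open-ended criterion is still applied with the arm known.

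A reader might go further than the documents allow in four ways:
- That the bias favours FTSG. Nothing in the text fixes a direction.
- That the mesh harms listed in the Background make surgeons abandon a mesh. They are listed as complications of using mesh, not as operative findings that rule it out.
- That excluded patients are those at highest risk. This is plausible for difficult abdomens, but no passage says so, and a patient with no implant cannot have an implant complication.
- That their complications never reach the safety data. Data up to exclusion may be kept {18b, 22}; later follow-up is what is lost.

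The phrase about analysing as per protocol could also be read loosely as meaning according to the protocol. Under a heading on non-adherence, and followed by a defence of leaving out non-recipients, that reading is weak.

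**Conclusion.** The point holds as a defect in how the primary comparison is protected, not as a demonstrated bias. The only population named is per protocol, the exclusion is a post-allocation judgement made with the arm known, and the balance argument is sound only for events before the envelope is opened. Under the assumptions of step 5, the false-positive rate in favour of either arm runs from no material change to about 7%, against a nominal 2.5% per direction. The 7% is a one-arm worst case, and a 75/25 split gives 4.4%. With no exclusion rate in the documents, where the trial would fall in that range cannot be said. It should still be corrected, because follow-up that was stopped cannot be recovered at analysis.

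**What to change.** 1. In {20c}, make the primary analysis intention-to-treat: every patient whose envelope was opened is analysed in the allocated arm, whatever was done. Patients with an anaesthetic complication before the envelope is opened may be left out.
2. In {11b}, state that a patient whose allocated repair is abandoned stays in follow-up with complications recorded. This does not alter when the surgeon may abandon the procedure.
3. Keep per protocol as a sensitivity analysis.
4. Limit the sentence on chance in {20c} to events before the envelope is opened.

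The cost is a change of wording and follow-up of a few more patients. The statistical price is dilution if several procedures are abandoned, of the size shown in step 6. Outcomes still missing for patients who withdraw consent are not solved by this change.

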### Sample size {14}

The power calculation is based on the primary outcome with an estimated short-term complication rate of 15% in the FTSG-group and in 40% in the synthetic mesh group. To achieve 80% power and 95% significance level, 39 patients are required in each arm. To compensate for loss to follow-up over the relatively long follow-up time, we plan for 90 patients (45 in each arm) to be included in the trial.

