### Plans to promote participant retention and complete follow-up {18b}

Patients will be sent an appointment for clinical follow-up by mail. Administration of patient follow-up will be conducted by a research nurse with overview of the entire study population (checklists). All data that has been collected up to the point of discontinuation will be considered consensual and used in the analyses. After discontinuation no further data will be collected from the study participant which will be considered “lost to follow-up”.

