#### Health economics

Data are presented descriptively and the results from each study group are analysed with Mann-Whitney *U* test or Student’s *t* test depending on the distribution of the specific variable.

The study assumes a significance level of 0.05.

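### The plan compares raw proportions out to 36 months and rules out any method for losses, so the 12- and 36-month complication and recurrence rates are open to bias that spare patients cannot remove

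*Protocol article*

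**What the plan says.** The Outcomes section {12} makes the surgical complication rate at 3, 12 and 36 months the primary outcome. Recurrence is a secondary outcome, with scheduled ultrasound at 12 and 36 months (Table 1). For both, the section on rates of complications and recurrences says: "Data are presented descriptively and the results from each study group are compared with chi-squared test".

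On losses, section {20c} says: "No statistical methods are used to compensate for missing data or loss to follow-up". It adds that the power calculation tolerates up to 12 missing patients in all. The sample size section {14} assumes "an estimated short-term complication rate of 15% in the FTSG-group and in 40% in the synthetic mesh group", asks for 39 per arm, and because of losses over the long follow-up adds that "we plan for 90 patients (45 in each arm) to be included in the trial".

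Section {18b} says: "All data that has been collected up to the point of discontinuation will be considered consensual and used in the analyses". Nothing is collected after discontinuation, and the patient is then classed as lost to follow-up. No section says whether such a patient stays in the 12- or 36-month denominator. The additional analyses {20b} are exploratory regressions on patient characteristics. No time-to-event analysis and no sensitivity analysis for losses is described.

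**The concern.** Over three years some patients will die, withdraw or stop attending, and the protocol enlarges the trial for that reason. Extra patients restore precision. They do nothing if those who leave differ from those who stay, or if the counting rule distorts the rate.

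The sentence in {20c} is an exclusion, not detail left to an analysis plan: an analysis plan that added a method would contradict the protocol. The argument in {20c} that chance balances non-adherence concerns only patients who could not be operated on. It does not cover losses between discharge and 36 months.

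Two further features raise the stakes. The Background, Outcomes and Discussion sections all say that complications of repair can be fatal. A patient who dies of one cannot attend a later visit, so some loss may be tied to the primary outcome. Section {17a} says the data analysts are not blinded, so an open denominator rule could be settled by someone who knows the allocation.

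**Working it through.** **Inputs from the protocol.** Complication rates 15% and 40%; 39 per arm required; 45 per arm enrolled; up to 12 missing; chi-squared test; no method for losses.

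**The plan's own figures.** 90 − 2 × 39 = 12, and 12/90 = 13.3%. The 39 reproduces with the pooled normal formula and a one-sided 5% test: (1.645 × √(2 × 0.275 × 0.725) + 0.842 × √(0.15 × 0.85 + 0.40 × 0.60))² / 0.25² = 38.4, so 39. The protocol does not state sidedness. That is a separate matter and nothing below depends on it.

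**Assumptions.** The documents give only short-term rates. I take 15% and 40% as the true 36-month risks, with constant event and loss hazards, and first with loss unrelated to outcome. The even split of 12 losses (6 per arm) is also mine.

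**Step 1: equal loss, L = 13.3% per arm.** Let a = −ln(1 − p), b = −ln(1 − L) and A = 1 − (1 − p)(1 − L).
- Events seen before loss: E = a/(a + b) × A
- Lost while event-free: C = b/(a + b) × A

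FTSG: a = 0.1625, b = 0.1431, A = 0.2633, E = 0.1400, C = 0.1233.
Mesh: a = 0.5108, b = 0.1431, A = 0.4800, E = 0.3750, C = 0.1050.

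| Counting rule | FTSG | Mesh | Difference (points) |
|---|---|---|---|
| Lost patients count as event-free (E) | 14.0% | 37.5% | 23.5 |
| Event-free losses dropped, earlier events kept (E/(1 − C)) | 16.0% | 41.9% | 25.9 |
| Only patients assessed at 36 months | 15.0% | 40.0% | 25.0 |
| Censored at loss (time-to-event) | 15.0% | 40.0% | 25.0 |

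**Step 2: loss differs by arm** (assumed 3/45 FTSG, 9/45 mesh; still 12 in all).
- Lost = event-free: 14.5% against 36.2%, difference 21.7 points.
- Event-free losses dropped, earlier events kept: 15.5% against 43.0%, difference 27.5 points. (Simulation with a million patients per setting gave 27.6.)
- Assessed only, or censored: 25 points.

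The same trial thus gives results about 6 points apart depending on an unstated rule.

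**Step 3: loss depends on outcome** (6/45 per arm, only assessed patients counted). If patients with an event are lost r times as often as those without, loss without an event is l = L/(pr + 1 − p), and the observed rate is p(1 − rl)/(1 − L).
- r = 3: 12.0% and 35.9%, difference 23.9 points.
- r = 1/3: 16.5% and 43.4%, difference 26.9 points.
- r = 1/3 in FTSG and 3 in mesh: 35.9 − 16.5 = 19.4 points. The reverse: 43.4 − 12.0 = 31.4 points.

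**Step 4: extreme bounds.** Illustrative data of 6/39 against 16/39, six lost per arm, chi-squared without continuity correction:

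| Lost patients | FTSG | Mesh | Difference (points) | p |
|---|---|---|---|---|
| Ignored | 6/39 | 16/39 | 25.6 | 0.012 |
| All event-free | 6/45 | 16/45 | 22.2 | 0.014 |
| All FTSG losses events, no mesh losses events | 12/45 | 16/45 | 8.9 | 0.36 |
| The reverse | 6/45 | 22/45 | 35.6 | 0.0003 |

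**The case against.** A reader might infer that the later rates are biased however lost patients are counted, because a chi-squared test forces a choice between dropping event-free losses and calling them event-free. The documents do not support that. Counting only patients assessed at the visit is a third option, and it is unbiased when loss is unrelated to outcome (Step 1).

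A reader might also take {18b} to mean that a 3-month event in a patient lost later must enter the 36-month numerator. That section says only that earlier data are used; they could serve the earlier visits alone.

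The size is easily overstated too. The short formula p/(p + (1 − p)(1 − L)) gives 0.40/0.92 = 43.5% for mesh. It keeps events that happen after loss and would never be seen; with losses spread over time the figure is 41.9%. The 12 is what the power calculation tolerates, not a forecast. Blinding of patients and follow-up surgeons makes strongly arm-dependent loss less likely. If most complications occur early, the bias in complication rates is smaller than shown. The bounds in Step 4 are extremes that any trial with similar losses would show.

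Finally, censoring needs loss unrelated to outcome, as counting only assessed patients does, so a time-to-event estimate alone is no cure.

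All of this stands, and it narrows the point. It does not justify an explicit refusal of any method, with no stated denominator and no sensitivity analysis, for outcomes followed over three years.

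**Conclusion.** The point holds in a limited form and should be acted on. The protocol excludes any handling of losses, leaves the later denominators open and relies on spare patients, which do not address bias.

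With 13.3% loss, equal by arm and unrelated to outcome, the bias is about 1 point (FTSG) to 2.5 points (mesh) in either direction, or nil, depending on the counting rule. That alone would rarely change the conclusion. The material risk is loss that differs by arm or depends on outcome: the scenarios above move a true 25-point difference to between 19.4 and 31.4 points, and the extreme bounds run from about 9 points, no longer significant, to about 36.

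These sizes rest on short-term design rates used as 36-month rates, on constant hazards and on assumed loss patterns. They show how far the result could move, not that it will. The same reasoning applies to recurrence, for which the protocol gives no design rate. The choice of a per-protocol analysis set and the sidedness of the sample size are separate questions.

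**What to change.** Replace the sentence in {20c} with wording such as: *Complications and recurrence to 12 and 36 months will be estimated by arm as cumulative incidence, with patients censored at last contact and death not due to a complication treated as a competing event (for recurrence, any prior death); the difference between arms will be given with a 95% confidence interval.*

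In addition:
- For any visit-based chi-squared test, state who is in the denominator and whether events seen before loss are carried forward.
- Add a best/worst-case or tipping-point sensitivity analysis at 3, 12 and 36 months. This is the part that deals with outcome-related loss.
- Record on the case report form the date of each complication and of last contact.

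The cost is a little more analysis work and the date fields; the sample size and visit schedule are unchanged. Two limits remain. Recurrence dates are known only to the interval between visits, so that estimate is interval-censored. Censoring still assumes loss unrelated to outcome, which is why the sensitivity analysis is needed alongside it.
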